### Adverse events

We define adverse events as unfavorable or unintended signs, symptoms or disease occurring after treatment that are not necessarily related to the moxibustion intervention. In every visit, adverse events will be reported by participants and examined by the practitioner.

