### Outcome

Ministry of Health of the People's Republic of China (MHPRC) has proposed a series of criteria to define patient response in the context of clinical trials of KOA, known as the guiding principle of clinical research on new drugs (GPCRND) [25]. According to these criteria, a patient with KOA is assessed including pain, the relation between activity and pain, function impairment, and special exams (Table 1). This scoring system was previously validated. The degree of KOA is divided into three level: mild- < 5 score;moderate-5 ~ 9 score; severe-> 9 score.

**Table 1 T1:** List of GPCRND-KOA

Item	Grade/Classification	Score
Pain or discomfort in night when lying in bed	No	0
	Pain in activity or some position	1
	Pain in non-activity	2
Morning stiffness or pain worse when getting out of bed	No	0
	< 30 minutes	1
	≥ 30 minutes	2
Pain or discomfort in walk	No	0
	After walking in some distance	1
	Pain at beginning of walk or worse	2
Arise from seat	Independent	0
	Need assistance	1
The maximum walk distance(accompany with pain)	Unrestricted	0
	Restricted, > 1 km	1
	300 m ~ 1 km	2
	< 300 m	3
Daily Activities	Board standard airstairs	
	Independent	0
	Difficulty	1
	Unable	2
	Step down standard airstairs	
	Independent	0
	Difficulty	1
	Unable	2
	Squat or bend knees	
	Independent	0
	Difficulty	1
	Unable	2
	Walk over rough terrain	
	Independent	0
	Difficulty	1
	Unable	2

Therapeutic effect was assessed by comparing baseline and final conditions reported by the patient. Four categories were listed as below: clinical response-no symptom, normal function activity, clinical symptom score reduction ≥ 95%; markedly effective-no obvious symptom, normal joint function activity, able to participate in activity and work, clinical symptom score reduction 70 ~ 95%; improved-no pain, normal joints' flexion and extension, improvement in activity and work, clinical symptom score reduction 30 ~ 70%; ineffective-not arrived at the above standard involving with symptom and function impairment, clinical symptom score reduction < 30%.

This trial also records adverse effects reported by patients during treatment. The outcome measures above will be assessed before the treatment, the 30 days of the last moxibustion session and 6 months after the last moxibustion session.

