### Design

A multi-centre (four centers in China), randomised, subject blinded(group A and B) and assessor blinded, positive controlled trial will be conducted at the Jiangxi Traditional Chinese Medicine Hospital in Nanchang, The first Affiliated Hospital with Anhui University of TCM in Hefei, Jiangsu Traditional Chinese Medicine Hospital in Nanjing, and Shanxi Traditional Chinese Medicine Hospital in Xian. The study will be sequentially conducted as follows: a run-in period of one week prior to randomisation, a treatment period of 30 days (5 sessions per week), and a follow-up period of six months. The total study period will be eight months. At the end of the run-in period, participants will be randomised to the heat-sensitive moxibustion group, the conventional moxibustion group, or the conventional drug treatment group by the central randomization system (Figure 1).This system is provided by China Academy of Chinese Medical Sciences, which adopted the computer telephone integration (CTI) technology to integrate computer, internet and telecom. The random number list will be assign by interactive voice response (IVR) and interactive web response (IWR)[26]. The success of blinding will be assessed at each participant's last visit. Researchers who did not participate in the treatment and who are blinded to the allocation results will perform the outcome assessment

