### Treatment protocol

#### Heat-sensitive moxibustion

Moxibustion will be performed by certified acupuncture medical doctors at four centers. Qualified specialists of acupuncture in traditional Chinese medicine with at least five years of clinical experience will perform the acupuncture in this study. All treatment regimens will be standardized between four centers practitioners via video, hands-on training and internet workshops. Participants will be randomly assigned to the heat-sensitive moxibustion group, the conventional moxibustion group, or the conventional drug group. In the former groups, a 22 mm (diameter) × 160mm (length) moxa-sticks (Jiangxi Traditional Chinese Medicine Hospital, China) will be used. The patient is usually in the comfortable supine position for treatment, with 24°C ~ 30°C temperature in the room. He should be wearing loose trousers, especially making his knee joints exposed.

For the heat-sensitive moxibustion group, the moxa-sticks are lit by the therapist and held over the region consisting of Yin Lingquan(SP9), Yang Lingquan(GB34), Liang Qiu(ST34), and Xue Hai (SP10). The warming suspended moxibustion about distance of 3cm are used to search the acupoint heat-sensitization phenomenon. The following patients sensation will suggest the special heat-sensitization aupoint: diathermanous sensation due to moxa-heat, defining as the heat sensation conducting from the moxa local skin surface into deep tissue, or even into the joint cavity; expand heat sensation due to moxa-heat, defining as the heat sensation spreading the surrounding little by little around the moxa point; transfer heat sensation due to moxa-heat, defining as the heat sensation transferring along some pathway or direction, even to the ankle or hip conduction; non-heat sensation due to moxa-heat. When some acupoint exists one below sensation at least, the therapists mark the point as heat-sensitive acupoint. We try our best to seek all the special acupoints in each patient by the repeated manipulation.

The therapists begin to treat patients from the most heat-sensitive intensity acupoint. Treatment sessions end when patients are feel the acupoint heat-sensitization phenomenon disappeared. Generally speaking, we find the time range from 30 ~ 60 minutes.Patients receive the treatment two times/day in 1^st ^week(two times/day from 2^nd ^week ) for a total of 35 sessions over 30 days.

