#### Conventional drug group

Now, intra-articular hyaluronan (HA) or hylan is popular approved for the treatment of KOA [27]. A number of systematic reviews have published positive evidence of efficacy and safety of intra-articular HA for KOA. For example, a recent review proved HA to be an effective, safe, and tolerable treatment for symptomatic KOA [28]. Therefore, this protocol selected Sodium Hyaluronate Injection Intra-articula as the conventional drug. The injection will be used six days a time (2ml) as a total of five times.

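### If treatment sessions count as visits, the moxibustion arms get up to seven times as many occasions to report adverse events as the injection arm, and the recording window is stated in two different ways

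*Protocol article*

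**What the plan says.** The Adverse events section ties collection to contact and names the examiner: "In every visit, adverse events will be reported by participants and examined by the practitioner". It defines events as unfavourable or unintended "signs, symptoms or disease occurring after treatment that are not necessarily related to the moxibustion intervention".

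The Outcome section lists adverse effects beside the efficacy measures: "This trial also records adverse effects reported by patients during treatment". It then gives assessment times shared by all arms: before treatment, a 30-day time point and six months.

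Contacts differ by arm. The two moxibustion sections each schedule treatment "for a total of 35 sessions over 30 days". The Conventional drug group section states: "The injection will be used six days a time (2ml) as a total of five times". The Design section gives another frequency for the treatment phase: "a treatment period of 30 days (5 sessions per week" in its words.

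On blinding, the Design section says: "Researchers who did not participate in the treatment and who are blinded to the allocation results will perform the outcome assessment". Participants are blinded in A and B only.

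**The concern.** When events are collected at each contact and one arm has many more contacts, the recorded rate depends on how often people are asked as well as on what happened to them. Brief, mild complaints are the most affected, because they may be forgotten by a later contact.

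The examiner matters too. The trial has blinded assessors who do not treat, yet adverse events go to the practitioner. The Heat-sensitive moxibustion section uses that word for the people whose treatment delivery is standardised across centres. The examiner is therefore probably the treating clinician, who knows the arm.

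The recording window is also unclear. One section covers the treatment period; the other speaks of events after treatment. If the first is followed, events in the six-month follow-up go unrecorded.

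What is at stake is the reading of harms. The Background motivates the trial partly by side effects of conventional drugs, and the Discussions section justifies sodium hyaluronate partly by its fewer adverse reactions. Readers will set the arms' adverse-event rates side by side whether or not a test is planned.

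**Working it through.** **Inputs.** 35 sessions in A and in B (the two moxibustion sections); 5 injections in C (Conventional drug group); 5 sessions per week over 30 days (Design); 144 participants per arm (Sample size).

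**Step 1: the session count.** The stated total of 35 does not follow from the printed frequencies. Twice daily for 30 days gives 2 × 30 = 60. Five sessions per week gives 5 × 30/7 = 21.4. A total of 35 results from, for example, twice daily for 5 days and then once daily for 25 days (10 + 25), but the text prints twice daily for both phases. These passages must be reconciled. I use the stated total and show the Design figure beside it.

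**Step 2: ratio of reporting occasions, A or B against C.**

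| What counts as a visit | A or B | C | Ratio |
|---|---|---|---|
| Every session, stated total | 35 | 5 | 7.0 |
| The same, plus two post-treatment assessments | 37 | 7 | 5.3 |
| Every session, Design frequency | 21.4 | 5 | 4.3 |
| Study visits only | equal | equal | 1.0 |

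A against B is 35/35 = 1 throughout.

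**Step 3: what unequal contact could do.** The documents give no adverse-event rate and no chance of reporting, so both are assumed here. Let the true risk be the same in all arms, and let q be the chance that an event is picked up at any one contact. The share of events recorded over k contacts is 1 − (1 − q)^k.

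| q (assumed) | k = 35 | k = 5 | Ratio |
|---|---|---|---|
| 0.02 | 50.7% | 9.6% | 5.3 |
| 0.05 | 83.4% | 22.6% | 3.7 |
| 0.10 | 97.5% | 41.0% | 2.4 |
| 0.30 | 100% | 83.2% | 1.2 |
| 0.50 | 100% | 96.9% | 1.03 |

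At about 21 contacts and q = 0.05 the share is 1 − 0.95^21 = 65.9%, so the ratio to C is 65.9/22.6 = 2.9.

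**Step 4: consequence for a comparison of rates.** Take an assumed true risk of 20% in both arms. At q = 0.05 the recorded rates are 0.20 × 83.4% = 16.7% and 0.20 × 22.6% = 4.5%. With 144 per arm, a two-sided 5% test of two proportions would call this false difference significant about 92% of the time. At q = 0.30 the recorded rates are 20.0% and 16.6%, and the figure falls to about 11%.

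The model is generous to the concern. It lets every contact detect the event, including contacts before it occurred, and it treats contacts as independent even when two fall on one day.

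**Step 5: the two windows.** The Outcome section limits recording to the treatment period. The Adverse events section defines events as occurring after treatment. Read literally, the two do not overlap. If *after treatment* means after treatment has begun, they overlap for the 30 days but still differ over the six-month follow-up. The definition also names only the moxibustion intervention, although one arm receives injections.

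**The case against.** The strongest reply is that *visit* need not mean *session*. The article calls treatments sessions throughout, and its only other use of *visit* is the participant's last one, when blinding is checked. Adverse effects sit under Outcome, just before assessment times common to all arms. On that reading the ratio is 1 and the imbalance disappears. This stands as a possible reading, but recording during treatment points the other way, and four centres could apply the rule differently.

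Second, the objective is effectiveness and no between-arm safety analysis is described. This stands. The risk falls on any comparison of rates that is made, including a descriptive one; no stated analysis is wrong. The absence of a safety analysis from a condensed article is not itself a fault.

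Third, a reader might go further and infer a certain sevenfold bias. For instance, if each contact is an independent 1% chance of a new complaint, 1 − 0.99^35 = 30% of patients would have an event against 1 − 0.99^5 = 5%, and almost every trial of this size would show a false difference. The documents do not support that. All arms are treated over about the same 30 days, and a participant can mention at one contact something that arose since the last. What matters is how often an event goes unreported until asked about, and step 3 shows the effect nearly vanishing when reporting is reliable.

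Fourth, that the practitioner is the treating one is an inference, and having a clinician examine events is not in itself an error. Both stand, although the inference is well supported.

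Fifth, the definition's reference to moxibustion removes a causality requirement and does not exclude C. This is fair; the wording needs tidying, but it is not evidence that C's events are ignored.

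**Conclusion.** The point holds in a limited form. Followed as written, and with sessions counted as visits, the rule gives A and B up to 7 times as many reporting occasions as C, or about 4 times at the Design frequency. It would tend to inflate minor, transient events on moxibustion relative to injection. The size cannot be derived from the documents: under the assumed values the ratio of recorded events runs from 5.3 at very low detection to 1.03 at high detection. Persistent or serious events would be little affected.

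The A against B comparison, which the Discussions section calls the more interesting one, is unaffected in contact frequency. Examination by someone who probably knows the arm adds a risk of unknown direction. The conflicting windows need correcting however *visit* is read. Nothing here touches the efficacy analysis. It is worth changing because the change is cheap.

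**What to change.** - Define *visit* for adverse-event collection. Keep session-level collection for safety monitoring, and list those events separately without comparing arms.
- Base any between-arm comparison on one standard question put to all three arms at the common end-of-treatment and six-month assessments. Those times are now counted from the last moxibustion session, so state the matching dates for C.
- Ask the question after the outcome has been scored, or have existing staff other than the outcome assessor ask it. Skin or injection-site complaints could otherwise reveal the arm to the blinded assessor.
- Reconcile the Outcome and Adverse events sections to one recording window, from first study treatment to the six-month visit, and refer to study treatment in place of the moxibustion intervention.

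The cost is one short form at assessments already planned, with no extra visits or staff. The downside is that brief, mild events are recalled less completely, and possibly not equally across arms, because participants in C are not blinded.

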### Ethics

Written consent will be obtained from each participant. This study was approved by all relevant local ethics review boards. Ethics Committee of Affiliated hospital of Jiangxi Institute of Traditional Chinese Medicine had approved this trial: code issued by ethic committee is 2008(9).

## Discussions

To our knowledge, although there is no cure for KOA, current kinds of therapies focus on the relief of pain and stiffness and maintenance or improvement in functional status and quality of life as important goals. A number of clinical trial suggested moxibustion as one of traditional acupuncture therapy, should effective in the treatment of KOA. But the methodological problems of published trials haunt us the trust of moxibustion. Therefore, we design this rigorous clinical trials meeting the CONSORT statement and guidelines to guarantee a high internal validity for the results. In view of the special nature of the KOA itself, positive control should be selected to solve the patient's pain, swell, and impairment. At present, various conventional medications are used to slow down and control with the disease. Although Anesthetic and NSAIDS can relive the pain and inflammation, patients are not considered it as priority options because of multiple adverse reactions. Sodium Hyaluronate acid injections may give you more pain relief than oral medicines, and less adverse reactions. Therefore, we used the Sodium Hyaluronate acid injections as drug treatment in the protocol.

Actually, the aim of this trial contains two parts: "Is moxibustion treatment superior to Sodium Hyaluronate acid injections for KOA? And is heat-sensitive moxibustion superior to conventional moxibustion for KOA?" The latter one is our more interesting goal. According to the current theory of traditional Chinese medicine, moxibustion resulting from the burning of moxa, produces the radiant heat and drug effects to acupoints. This treatment penetrates deeply into the body, restoring the balance and flow of vital energy or life force through acupoints. So the selected of location for manipulating Moxa plays an important role in obtaining good effects. Generally speaking, the location acupoints are fixed along meridians. The conventional moxibustion is promoted for improving general health and treating diseases by stimulating these fixed acupoints. And doctors consider hyperaemia due to local skin vasodilatation as the indicator of moxibustion's effect. However, our clinical experience and observation in the past suggested that stimulating these fixed acupoints might not the best treatment site for moxibustion. In the human being there are two functional states, sensitization state and rest state. When the human body has disease, acupoints on the body surface may be sensitized with various types of sensitization, and acupoint heat-sensitization is a type of acupoint sensitization. acupoint is more than fixed skin site but external sensitive point reflecting the diseases. Therefore, acupoint is variable and depends on the pathological state. Traditional fixed acupints are thought as indicators to searching specific sensitive acupoint. That is, traditional fixed acupints don not consider the state as the key factor to local the acupoint, so the course of fixing the position is imprecisely.

When we light the moxa hold over the heat-sensitive acupoints, the patients will produce some heat-sensitization phenomenon. The following patients sensation will suggest the special heat-sensitization aupoint: diathermanous sensation due to moxa-heat, defining as the heat sensation conducting from the moxa local skin surface into deep tissue, or even into the joint cavity; expand heat sensation due to moxa-heat, defining as the heat sensation spreading the surrounding little by little around the moxa point; transfer heat sensation due to moxa-heat, defining as the heat sensation transferring along some pathway or direction, even to the ankle or hip conduction; non-heat sensation due to moxa-heat.

It is well-known that acupuncture and moxibustion originated from China several thousands years ago. The Inner Canon of Huangdi or Yellow Emperor's Inner Canon is an ancient Chinese medical text that has been treated as the fundamental doctrinal source for Chinese medicine for more than two millennia and until today. According with its core viewpoint and theory, acupoint is described and understood with the state , which is certain area of the skin in the course of diseases. "*Said section (acupoint) who shen-qi out of the procession itself, not flesh bones *"(Huang Di Neijing, Lingshu, Chapter: jiu zhen shi er yuan).That is, acupoints are not flesh bones, which have their particular morphology and fixed location, but dynamic functional state due to shen-qi's activity. "*when five internal organs are suffering from diseases, we can use 12 yuan-acupoints to treat. These acupoints are derived from five internal organs intrinsic nature. Five internal organs are diagnosed by 12 yuan-acupoints. Different organs accord with relative yuan-acupoint. We can observe and distinguish the acupoint response to external stimulation. Then, the disease from five internal organs can be diagnosed and treated by 12 yuan-acupoints" *(Huang Di Neijing, Lingshu, Chapter: jiu zhen shi er yuan).So an important view was expressed by this sentence, that is, acupoints reflect the internal diseases and can be operated in treatment of disease with the functional role. In physiological status, people do not always become aware of the existence of acupoint. In contrast, patients can feel some changes from acupoint involving with diseases in pathological state. So the ancient persons located the acupoints through the state changes. "*Lung shu-acupoints locate nearby the third vertebrae; Heart shu-acupoints locate nearby the fifth vertebrae; Ge shu-acupoints locate nearby the seventh; Liver shu-acupoints locate nearby the ninth vertebrae; Spleen shu-acupoints locate nearby the eleventh vertebrae; Kindey shu-acupoints locate nearby the fourteenth vertebrae. These acupoints are far from about three-inch by spinal crest. If you want to search our acupoints exactly, the finger's touch and press are must be use above the skin and we obtain the sensation from patients, such as pain. " *(Huang Di Neijing, Lingshu, Chapter: back shu). Back shu acupoints are searched by doctor through external stimulation. "If a patient is coughing with shoulder, we can select the lateral chest shu acupoints to treat. The shu acupoints are nearby from *the third vertebrae to the fifth vertebrae. Press the location, patients will be comfortable at once. Then we needle the location, which is acupoint actually*." (Huang Di Neijing, Lingshu, Chapter: five xie) *We conclude that *sensitized status is key factor to locate the position of acupoints.

Among the changes, sensitized status is the common one, described that acupoints on the body surface may be sensitized with various types of sensitization. This sensitized acupoint is not only the pathological phenomenon reflecting the diseases but also stimulating location with acupuncture and moxibustion. Acupoint heat-sensitization is a type of acupoint sensitization, which derived from our clinical experience and research in past twenty years. The special acupoint makes accordance with the classical thought and theory from the Inner Canon of Huangdi.

Our empirical evidence engaged us to formulate the following hypothesis: selecting the heat-sensitized acupoint may obtain therapeutic effect far better than acupuncture and moxibustion at acupoints of routine rest state. The main aim of this trial is to test and verify the hypothesis. If we can confirm this hypothesis, promoting moxibustion clinical efficacy would be carried our in this extraordinary way. It is of great significance to develop the theory of acupuncture and moxibustion.

Therefore, the purpose of this trial is more than discuss the efficacy of moxibustion as treatment. The results of our trial will be helpful to supply the evidence on the rules of heat-sensitive moxibustion location in China.
